##### **Basic design (including sample size)**

Date of First Randomisation: 18 March 2005

Date of Last Randomisation: 28 November 2008

Target for Randomisation: 600

Number Randomised: 641

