##### **Sample size calculation taken from the protocol (v5.2)**

The following is quoted from the PACE trial protocol (v5.2) (see also [13]) and describes sample size estimation based on percentages responding to the trial interventions. The primary outcomes were changed subsequently to measures on continuous scales.

At one year we assume that 60% will respond with CBT, 50% with GET, 25% with APT, and 10% with SSMC. The existing evidence suggests that at one-year follow-up, 50 to 63% of participants with CFS/ME had a positive outcome, by intention to treat, in the three RCTs of rehabilitative CBT [39-41] with 69% improved after an educational rehabilitation that closely resembled CBT [44]. This compares with 18 to 63% improved in the two RCTs of GET [42,43] and 47% improvement in a clinical audit of GET [45]. For usual medical care 6 to 17% improved by one year in two RCTs [40,41]. There are no previous RCTs of APT to guide us, but we estimate that APT will be at least as effective as the control therapy of relaxation and flexibility used in previous RCTs, with 26 to 27% improved on primary outcomes [39,43].

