Our planned intention to treat analyses will compare APT against SSMC alone, and both CBT and GET against APT. Assuming α = 5% and a power of 90%, we require a minimum of 135 participants in the SSMC alone and APT groups, 80 participants in the GET group and 40 in the CBT group [46]. However these last two numbers are insufficient to study predictors, process, or cost-effectiveness. We will have low statistical power to detect the difference between CBT and GET, though our estimates will be useful in planning future trials. As an example, to detect a difference in responder rates of 50 and 60%, with 90% power, would require 520 participants per group; numbers beyond a realistic two-arm trial. Therefore, we will study equal numbers of 135 participants in each of the four arms, which gives us greater than 90% power to study differences in efficacy between APT and both CBT and GET. We will adjust our numbers for dropouts, at the same time as designing the trial and its management to minimise dropouts. Dropout rates were 12 and 33% in the two studies of GET [42,43] and 3, 10, and 40% in the three studies of rehabilitative CBT [39-41]. On the basis of our own previous trials we estimate a dropout rate of 10%. We therefore require approximately 150 participants in each intervention group, or 600 participants in all. Calculation of the sample size required to detect economic differences between intervention groups requires data on cost per change in outcome, which are not currently available.

##### 

**Stratification at randomisation** Allocation of interventions to participants was by minimisation with a random component [47] and four stratification factors:

Centre (6 strata): 1 and 4, 2, 3, 5, 6, 7

CDC Criteria (2 strata): Met or unmet

London Criteria (2 strata): Met or unmet

Current Depressive Disorder (2 strata): Present or absent

Participants found to be incorrectly stratified will be kept in their original strata for the primary analysis in accordance with the principle of intention-to-treat (ITT) [48]. The extent of incorrect stratification will be reported.

#### **
*Data collection*
**

##### 

**Screening measures** A clinic patient log book was kept of all new CFS/ME referrals to trial centres to facilitate monitoring of recruitment to the trial. Screening information will not be used in the analysis except for:

1. Reasons for patients not taking part in the trial (see Participant Flow).

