The amount of item-missing data is expected to be minimal. However, if this is not so for any outcome scale then multiple imputation [58,59] at the item-level will be the primary method used. Items will be imputed 100 times [60] separately for each scale (with the exception of the CFQ and SF-36PF, which will be imputed simultaneously). All of the other items for that scale across all time points (including baseline), scores (overall and any subscales) across all time points (including baseline), the four stratification factors at randomisation, randomised intervention, main therapist, and main SSMC doctor will be included in the imputation model.

##### 

**Missing scale data** Missing baseline scale data are not an issue for the primary analysis of efficacy; no missing data are expected for the stratification factors. Where the CFQ or SF-36PF is missing at baseline they will be replaced by the relevant scale at screening. There is specific guidance for missing baseline scale data, and this will be followed [61]. That is, we will use mean imputation of baseline variables assuming baseline and outcome are correlated less than 0.6.

Where the amount of item-missing data is considered minimal, missing outcome scale-data will be handled within the primary analysis by maximum likelihood [57,62] under a similar model for the missing data mechanism assumed for missing item data (see section above). We will report the amount of missing scale data by the percentage of participants who have more than 10% missing item data for each scale reported.

##### **
*Loss to follow-up*
**

Some participants will withdraw from follow-up during the trial, and for these it may be more appropriate to assume data are missing not at random (MNAR). Where more than 10% of randomised participants are lost to follow-up, the impact of this will be investigated in a sensitivity analysis using the weighting approach described by Carpenter, Kenward and White [63] if multiple imputation is the primary method, or comparing selection model and pattern-mixture model therapy effect estimates [64] where maximum likelihood is the primary method.

##### **
*Method for handling multiple comparisons and multiplicity*
**

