##### **Health economics outcomes**

**Definition of outcome measures (including trial periods) Service use and lost employment** Comprehensive data are being collected on all health, social care and other relevant services used by individual study members using a tailored version of the Client Service Receipt Inventory (CSRI). The CSRI is used at baseline and at 24- and 52-week follow-up each time covering resource use for the previous 6 months. The CSRI covers the following broad categories of information.

• Living situation/accommodation

• Education, employment and income (including benefits)

• Time off work (measured in days) and time unemployed (or retired due to illness) summing the relevant cost period (−24 to 0 weeks, 0 to 24 weeks 0 to 52 weeks)

• Use of health and social care resources

##### 

**Cost calculation** The costs of each resource item will be calculated using best available unit cost estimates [75]. The cost of APT, GET and CBT will be estimated using information on the core resource inputs involved in delivering the interventions, and estimating country-specific costs for those inputs. Costs will be calculated using data on the number of intervention sessions received by each participant.

Lost employment costs for those in employment will be calculated by combining time off work with daily earnings. For those unemployed/retired due to ill health lost employment costs will be calculated by combining this period of time with average age and gender specific earnings.

The variables derived from the CSRI will be: (i) use (yes/no) of each service, (ii) number of service contacts/days in hospital, (iii) cost of each service, (iv) in employment (yes/no), (v) days not worked, and (vi) whether benefits received (each benefit - yes/no).

##### 

**Quality adjusted life year measurement** The EQ-5D consists of five domains (mobility, self-care, usual activities, pain/discomfort, and anxiety/depression). Each of these will receive a score of 1, 2 or 3 corresponding to no problems, moderate problems and major problems. Utility scores will be attached to each health state based on these scores (a table of utility values [76] has been produced by the Centre for Health Economics, University of York). These utility scores will be used to generate QALY gains over the follow-up period.

##### 

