##### **Primary analysis (including method of analysis)**

**Cost comparisons** Regression analysis will be used to compare service costs and total costs between the four interventions which will each be represented by dummy variables. Each intervention will be used in turn as the reference category to make all relevant comparisons.

##### 

**Predictors of cost** Participant characteristics will be used in a regression model to explain differences in baseline costs. We will test the hypothesised associations with both healthcare and societal costs, as well as using multivariable modelling of other possible predictors identified from univariate analyses. Subsequent regression models will be used to explain variations in follow-up costs, and these will also include clinical characteristics from preceding periods. Two types of regression model will be used. First, we will construct ordinary least squares models, with bootstrapping used to produce reliable 95% CIs around the regression coefficients. Second, we will construct generalised linear models with a log link and gamma distribution to account for the skewness that is likely in the costs data.

Independent variables will include demographic characteristics (such as age, gender and marital status), year of randomisation, clinical variables (such as fatigue score, disability, depression, anxiety) and benefits status (whether receiving benefits and whether benefits are in dispute).

##### 

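### The plan's missing-data strategy does not carry over to 52-week cost totals and QALYs: its expected route becomes a complete-case analysis that ignores observed 24-week costs and utilities

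*SAP article*

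**What the plan says.** The primary health economics objectives compare costs, cost-effectiveness and cost-utility up to 52 weeks; the 24-week horizon is secondary.

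- **Data.** Under Health economics outcomes: "The CSRI is used at baseline and at 24- and 52-week follow-up each time covering resource use for the previous 6 months". QALYs come from EQ-5D utilities. Table 2 schedules both instruments at baseline, 24 weeks, 52 weeks and discontinuation of therapy, but not at discontinuation of follow-up, where the fatigue and physical function scales are collected.
- **Analysis.** The Cost comparisons paragraph states: "Regression analysis will be used to compare service costs and total costs between the four interventions which will each be represented by dummy variables". The cost-effectiveness planes come from bootstrap resamples of the trial data. No repeated-measures term appears, and no rule for an absent CSRI or EQ-5D.
- **General missing-data strategy.** Missing item data sets one approach for all scales in the principal papers. If few items are missing, which is expected, scores are prorated and, under Missing scale data, "missing outcome scale-data will be handled within the primary analysis by maximum likelihood". Multiple imputation becomes the primary method only if item-missing data are not minimal. The MAR assumption is conditional on the variables in the analysis model.
- **Sensitivity analyses.** The economic ones vary the unit costs of informal care, lost employment and therapy. The MNAR analysis is listed under the primary clinical outcomes and applies when more than 10% are lost to follow-up, with loss defined on the primary outcome scales.

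**The concern.** Maximum likelihood helps with missing outcomes when the model holds other outcome records for the same person. The mixed model for fatigue and disability does: someone absent at week 52 still contributes weeks 12 and 24, and those scores inform the 52-week contrast under MAR.

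A 52-week cost total is a single number. If the second half-year is missing, the total is missing, and the regression has no other outcome record for that person. The 24-week cost, probably the best available predictor of the missing part, is not a covariate in the stated model. Conditioning on that model's variables therefore means conditioning on arm, perhaps with baseline CSRI cost. The same applies to QALYs and to a bootstrap of the joint cost and outcome differences.

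Imputation does not fill the gap, because missing items trigger it and a missing visit does not. Nor does the MNAR analysis: someone who returns the fatigue scale but no CSRI does not count as lost to follow-up. At stake are the precision and possibly the bias of the 52-week economic results, with no planned analysis that would show either.

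**Working it through.** **1. The plan's own figures.** Inputs from the sample size section: "At one year we assume that 60% will respond with CBT, 50% with GET, 25% with APT, and 10% with SSMC"; "Assuming α = 5% and a power of 90%, we require a minimum of 135 participants in the SSMC alone and APT groups"; "On the basis of our own previous trials we estimate a dropout rate of 10" per cent; "We therefore require approximately 150 participants in each intervention group, or 600 participants in all".

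For 25% v 10%, two-sided 5%, power 90%, pooled variance without continuity correction:

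n = [1.960 × √(2 × 0.175 × 0.825) + 1.282 × √(0.25 × 0.75 + 0.10 × 0.90)]² / 0.15² = (1.053 + 0.675)² / 0.0225 ≈ 133 per arm, against 135 stated.

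Dropout: 135 / 0.90 = 150 per arm; × 4 = 600. Both agree with the plan. The 10% is thus a planning allowance for clinical dropout, and no economic sample size was calculated.

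**2. Loss of precision.** From Basic design: "Number Randomised: 641". For an assumed proportion m without a complete 52-week record, the loss is 641 × m and the standard error rises by the factor 1/√(1 − m).

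| m (assumed) | Participants lost | SE increase |
|---|---|---|
| 5% | 32 | 2.6% |
| 10% | 64 | 5.4% |
| 15% | 96 | 8.5% |
| 20% | 128 | 11.8% |

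At 10%, 577 remain, about 144 per arm. A total needs both forms. With 5% missing at each visit, 90% to 95% are complete. With 10% missing at 52 weeks and 0 to 10% at 24 weeks, 80% to 90% are complete. The economic loss could therefore be below or above 10%.

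**3. Bias, by hand.** If those missing differ from those observed by d (in SDs of cost) and the missing proportions are m₁ and m₂, the complete-case bias in the arm difference has size |m₁d − m₂d|. The SE at 144 per arm is √(2/144) = 0.118 SD.

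- 10% v 10%, d = 0.5: bias 0.
- 5% v 15%, d = 0.5: |0.025 − 0.075| = 0.05 SD; 0.05/0.118 = 0.42 SE.
- 5% v 15%, d = 0.25: 0.025 SD, or 0.21 SE.

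**4. Bias, by simulation.** Assumptions, none of them from the documents: 160 per arm; two log-normal half-year costs with log-SD 0.8 and log-scale correlation 0.6; week-52 dropout depending on 24-week log cost with log-odds 0.7 or 1.0 per SD (odds ratios about 2.0 and 2.7); 2,000 trials per setting.

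| Dropout by arm | Complete-case bias / SE |
|---|---|
| 5% v 15% | −0.50, −0.72 |
| 10% v 20% | −0.47, −0.64 |
| equal 10% | about 0 |

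Independent reruns gave −0.54 and −0.73, and −0.48 and −0.70, for 5% v 15%. Imputing from the 24-week cost left at most 0.03 SE in absolute value.

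If baseline cost is adjusted for (correlation 0.6 also assumed), 5% v 15% gives −0.37 and −0.53. With adjustment and weaker assumptions, 8% v 12% gives −0.12 and −0.22, and 5% v 15% with odds ratio 1.35 gives −0.17.

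When dropout was unrelated to cost there was no bias. The SD of the complete-case estimate against the imputed one was then 0.275 v 0.262, 0.270 v 0.260 and 0.277 v 0.260, that is, ratios of 1.05, 1.04 and 1.07.

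**The case against.** The other side has several good points.

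- **Complete-case analysis is an inference.** The plan does not say that incomplete participants are dropped, and its general section is meant to cover all scales. Imputation could reach the CSRI or EQ-5D if enough items were missing. This stands, but the plan does not expect that route, and a missing visit would not trigger it.
- **A reader might infer that no 52-week total can be formed without the planned forms.** That is too absolute. Both instruments are collected at discontinuation of therapy, Research visit window definitions lets an earlier unscheduled visit stand in for a missing one, and therapy costs come from session counts. A missing 24-week utility could also be interpolated, though no such rule is stated. Still, an earlier CSRI covers the months before that visit, so it does not supply the costs up to week 52.
- **A reader might infer that someone with only the 24-week form is lost altogether.** That person still contributes to the secondary 24-week objectives.
- **A reader might take ordinary least squares and the gamma model as the stated models for comparing arms.** They are named under Predictors of cost; Cost comparisons says only that regression will be used.
- **Complete cases can be valid.** If missingness depends only on arm and the covariates in the model, the comparison is unbiased. The baseline adjustment paragraph brings in baseline CSRI data, although its wording is loose, and this reduces the bias in the simulation.

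That the source is an article explains little: it says the plan is reproduced almost as approved, and it treats missing clinical data at length.

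**Conclusion.** The point holds as a gap in method. On its expected route the strategy gives a complete-case analysis of 52-week costs and QALYs, leaves observed 24-week data unused, and has no economic sensitivity analysis for missing data.

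The size depends on assumptions. At 10% incomplete, the loss is about 64 of 641 participants and about 5% on the standard error. Bias is near zero with equal or cost-unrelated dropout. It is about 0.4 to 0.7 SE with 5% v 15% dropout strongly related to 24-week cost, the lower end with adjustment for baseline cost, and smaller under milder assumptions.

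Two stronger readings are not supported. One is that at least 10% will be lost: that figure is a planning assumption, and the documents give no missing rate for the CSRI or EQ-5D. The other is that the economic result is biased: this needs dropout that both differs by arm and depends on cost, and the documents show neither. This is a cheap improvement.

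**What to change.** Add a missing-data paragraph to the health economics section stating that:

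1. missing 24- and 52-week CSRI costs and EQ-5D utilities are multiply imputed separately by randomised arm, using baseline and all observed costs, utilities, CFQ and SF-36PF scores and the stratification factors;
2. 52-week totals and QALYs are formed after imputation;
3. imputation is combined with the bootstrap, so that confidence intervals, planes and acceptability curves carry the imputation uncertainty;
4. the complete-case result is reported as a sensitivity analysis, with the number of complete economic records by arm.

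The cost is a paragraph of text and modest programming. No new data are needed, and multiple imputation is already in the plan for item data. The result still rests on MAR, now conditional on a richer set of observed variables.

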3. APT has better cost-effectiveness and cost-utility than SSMC up to 24 weeks, and up to 52 weeks.

4. Both CBT and GET have better cost-effectiveness and cost-utility than SSMC and APT up to 24 weeks, and up to 52 weeks, but their cost-effectiveness does not differ substantially.

The secondary hypotheses are:

1. Higher healthcare costs are associated with being female, being older and having comorbid conditions, particularly mood disorders and having other symptom-based diagnoses.

2. Higher total societal costs are associated with being male, being younger, having more severe physical disability, pervasive passivity (measured by actigraphy), certain illness beliefs, and having comorbid conditions, particularly mood disorders and having other symptom-based diagnoses.

##### 

**Outcome measures** The primary outcome measures will be:

1. Fatigue Chalder Fatigue Questionnaire (CFQ) (Likert scoring) [29].

2. Physical Disability SF-36 physical function (SF-36PF sub-scale, Version 2) [30].

Secondary outcome measures include safety outcomes, efficacy outcomes and health economics outcomes.

Safety outcomes are:

1. Serious deterioration (primary) defined as one or more of the following up to 52 weeks:

a. SF-36 physical function score diminishing by 20 or more points between baseline and any two consecutive assessment interviews.

a. Participant-rated CGI change score of “much worse” or “very much worse” at two consecutive assessment interviews.

a. Withdrawal from therapy (APT, CBT, or GET) later than 8 weeks due to participant’s reported worsening of their condition.

a. A serious adverse reaction.

2. Serious adverse events (includes serious adverse reactions and suspected unexpected serious adverse reactions).

3. Serious adverse reactions (includes suspected unexpected serious adverse reactions).

4. Non-serious adverse events (includes non-serious adverse reactions); numbers, proportions, and examples.

5. Withdrawals from the interventions.

The four components of ‘serious deterioration’ will be reported in addition to the composite outcome.

Efficacy outcomes are:

1. Participant rated Clinical Global Impression (CGI) [31] change category.

2. Anxiety measured by HADS-A subscale of the Hospital Anxiety and Depression Scale [32].

3. Depression measured by HADS-D subscale of the Hospital Anxiety and Depression Scale [32].

4. Six-Minute Walking Test [33].

5. Work and Social Adjustment measured by WSAS [34].

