**Cost-effectiveness analysis** Cost-effectiveness will be assessed by linking data on service cost differences and outcome (fatigue and physical disability) differences [77]. If any intervention has significantly lower costs and significantly better outcomes then it will be deemed to be more cost-effective. If costs are significantly higher and outcomes significantly better or if there is uncertainty in these findings (indicated by the CIs) then we will use the net benefit approach and cost-effectiveness acceptability curves to assess cost-effectiveness. Cost-effectiveness results will be plotted on a cost-effectiveness plane. This will involve producing estimates of cost and outcome differences from 1,000 bootstrapped re-samples of the original data. Such planes will be produced for each combination of two-way group comparisons. The plane will inform us as to the probability that an intervention has either (i) lower costs and better outcomes, (ii) lower costs and worse outcomes, (iii) higher costs and better outcomes or (iv) higher costs and worse outcomes than each comparator.

##### 

**Cost-utility analysis** This will be conducted in the same way as the cost-effectiveness analysis but will use quality adjusted life years (derived from the EQ-5D) as the outcome measure.

##### 

**Predictors of cost-effectiveness/cost-utility** The net-benefit approach allows multivariable analyses of economic data. This will enable us to identify predictors of cost-effectiveness and cost-utility. This will be done using regression models as described above. In particular we hypothesise that age and gender will predict cost-effectiveness and cost-utility.

##### 

**Baseline adjustment** The predictors of the cost regression model will be adjusted by the CSRI baseline outcome data.

##### 

**Model assumptions checks** Cost data are usually skewed and if this results in similarly skewed residuals then the standard linear model is inappropriate. The distribution of the regression residuals will be checked visually and if the distribution is non-normal we will use bootstrapping with 10,000 resamples to estimate 95% CIs around the cost differences (CIs will be based on the percentile or bias-corrected method depending on the level of bias observed in the model.) The assumption of independent residuals will be checked by bootstrapping at the therapist level.

##### 

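### The net-benefit regressions for predictors of cost-effectiveness state no intervention-by-characteristic term, so as written they identify predictors of the level of net benefit, not of relative value

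*SAP article*

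**What the plan says.** All places are in the SAP article.

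- **Meaning of cost-effectiveness.** The cost-effectiveness analysis paragraph treats it as comparative: differences in cost are linked to differences in outcome, with a plane for each two-way comparison.
- **Predictors of cost-effectiveness/cost-utility.** The SAP says "The net-benefit approach allows multivariable analyses of economic data" and continues: "This will enable us to identify predictors of cost-effectiveness and cost-utility. This will be done using regression models as described above". It adds a hypothesis: "In particular we hypothesise that age and gender will predict cost-effectiveness and cost-utility".
- **The models described above (Predictors of cost).** There are two forms. One is stated as: "First, we will construct ordinary least squares models, with bootstrapping used to produce reliable 95% CIs around the regression coefficients". The other is a gamma GLM on the log scale, chosen because costs tend to be skewed. On covariates the SAP says: "Independent variables will include demographic characteristics (such as age, gender and marital status), year of randomisation, clinical variables", and benefits status is added. Neither intervention nor a product of intervention with a characteristic is listed.
- **Cost comparisons.** Here the four interventions do enter as dummy variables, each serving in turn as reference. No interaction is mentioned.
- **Objective served.** Secondary health economics objective 6 asks for characteristics that predict cost-effectiveness or cost-utility up to 24 and up to 52 weeks, for each intervention.
- **Cost hypotheses.** The first secondary health economic hypothesis reads in part: "Higher healthcare costs are associated with being female, being older and having comorbid conditions". The second concerns total societal costs and points the other way on both factors (male, younger).

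**The concern.** Cost-effectiveness in this SAP is a property of one intervention relative to another. A characteristic predicts it only if the incremental net benefit between two interventions changes with that characteristic, and in a regression that is an intervention-by-characteristic interaction. The stated models contain no such term, so their coefficients answer a different question: who has high or low net benefit whatever they were allocated.

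The answer to objective 6, and to the age and gender hypothesis, could then describe who is expensive or who does badly, and be read as saying for whom CBT, GET or APT is better value. The converse error is possible too: a characteristic whose effect reverses between arms can leave no trace in a pooled main effect.

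**Working it through.** The SAP gives no figure for this analysis, so there is nothing to reproduce. The check is algebra followed by an illustration of size.

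**1. Algebra.** Let NB = λE − C, with E the outcome, C the cost and λ the willingness to pay. Suppose a characteristic x adds c to cost in every arm and nothing to outcome. Then E[NB | arm j, x] = a_j − c·x.
- The coefficient on x is −c, whether arms are pooled or fitted separately.
- The incremental net benefit of arm j over arm k is (a_j − c·x) − (a_k − c·x) = a_j − a_k, the same at every x. The interaction is zero.

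The stated models therefore test c = 0, while the stated question is whether a_j − a_k varies with x.

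**2. Does another part of the SAP supply the term?**
- The cost-comparison dummies are main effects.
- Separate fits by arm, one reading of objective 6, each estimate −c. They bear on cost-effectiveness only if coefficients are compared across arms, and no such comparison is planned.
- The Subgroup analyses section asks whether intervention effects differ, but only by CDC criteria, London criteria and depressive disorder.

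**3. Size with no effect modification.** Inputs: N = 640 (4 × 160; the SAP reports 641 randomised), two-sided 5% test, and r, the correlation of x with net benefit. The values of r are assumptions. Noncentrality is δ = r√N / √(1 − r²), and rejection is about Φ(δ − 1.96), plus a negligible lower tail.

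| r with NB | δ, pooled | Pooled test rejects | Single arm (n = 160) rejects |
|---|---|---|---|
| 0.10 | 0.10 × 25.30 / 0.995 = 2.54 | 72% | 24% |
| 0.15 | 3.84 | 97% | 48% |
| 0.20 | 5.16 | 99.9% | 73% |

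**4. Simulation check.** Assumptions: 150 per arm (the SAP's target), a binary characteristic at 50% prevalence, normal errors, an equal shift in net benefit in every arm, 3,000 runs per setting.

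| Shift (SD) | Main effect flags x | At least one of four arm-specific fits flags x | Interaction test (3 df) flags x |
|---|---|---|---|
| 0 | 5.9% | 18.5% | 4.4% |
| 0.25 | 86% | 81% | 4.9% |
| 0.4 | 99.9% | 99% | 5.0% |
| 0.5 | 100% | 100% | 6.0% |

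The analytic value for 0.25 SD agrees: 0.25 / (2/√600) = 3.06, and Φ(3.06 − 1.96) = 86.5%.

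**5. Dilution by the outcome part.** The tables above set the association with net benefit itself. If x relates only to cost, outcome variance weakens it. With correlation 0.20 with cost, an outcome unrelated to x and to cost, and an outcome-value SD k times the cost SD, r with NB = 0.20 / √(1 + k²). At N = 640:
- k = 1: r = 0.141, rejection 95%
- k = 2: r = 0.089, rejection 62%
- k = 4: r = 0.049, rejection 23%

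**6. A real modifier that reverses.** Take slopes of +0.15 SD per SD of x in two arms and −0.15 in the other two, a difference of 0.3. The average slope is zero, so the pooled test rejects at its 5% level. The interaction test has noncentrality 640 × 0.15² = 14.4 on 3 df, which is 90% power.

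**The case against.** The strongest reply is that this reads silence as a wrong specification. The covariate list is open-ended in its wording, and it also serves a regression on baseline costs, where allocation has no place. The models described above could be taken to include the cost-comparison regression with its intervention dummies. Interactions are thus unstated, not excluded. That stands, and it limits the point. It does not remove it: on either reading, the one term that answers the question is not written down.

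A second reply is that objective 6 asks for predictors for each intervention, which arm-specific regressions answer descriptively. They do answer a question about net-benefit level. They do not fit the comparative meaning that the SAP itself gives to cost-effectiveness.

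A reader might go further and infer that age and gender will be declared predictors of cost-effectiveness simply because the SAP expects them to drive costs. The documents do not support that:
- The cost hypotheses are most naturally about baseline costs, which is where the SAP says it will test them.
- Their direction reverses between healthcare and societal costs.
- The Baseline adjustment paragraph adjusts the cost regression for baseline CSRI data. If carried over, this would weaken a stable link between age or gender and cost.
- An association with outcome could offset one with cost, and outcome variance dilutes it.

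The near-certain rejection rates in the working belong to assumed associations and are not forecasts for this trial.

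**Conclusion.** The concern holds as a gap in the stated model. Followed as written, the analysis can report a purely prognostic characteristic as a predictor of cost-effectiveness, and it can miss one whose effect reverses between arms. This follows from the algebra and needs no assumption about effect size.

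How often it would happen is not fixed by the SAP. Under the assumptions shown, it ranges from about 23% (correlation 0.20 with cost, outcome-value SD four times the cost SD), through about 72% (correlation 0.10 with net benefit), to near certainty at stronger associations. The interaction test stays at 4% to 6% in the simulated settings. Adjustment for baseline cost is not modelled and would probably lower the figures for the stated models.

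The point concerns a secondary health economics objective. The primary clinical contrasts, the cost comparisons, and the planned cost-effectiveness planes and acceptability curves are untouched.

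**What to change.** In the paragraph on predictors of cost-effectiveness/cost-utility, replace the cross-reference with a stated model: net benefit regressed on intervention dummies, the characteristic, and their products. Base any claim about a predictor of cost-effectiveness or cost-utility on the interaction terms, which are the change in incremental net benefit, for each pairwise comparison and over a range of willingness-to-pay values. Report characteristic main effects and arm-specific coefficients as predictors of net-benefit level only.

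The same edit should say which regression form applies. Net benefit can be negative, which a gamma model cannot take, so the second of the two cost models does not carry over unchanged.

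The cost is a sentence or two of SAP text and extra terms in models already planned. The statistical price is precision: interactions are estimated less precisely than main effects, so fewer predictors will be claimed.
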